#### Evaluation and follow-up

Clinical evaluation and trial documentation consist of seven visits: screening (V1), intervention (V2) and five postoperative follow-up examinations ending with V7 after 26 weeks (Table 1).

**Table 1 T1:** Visit schedule

**Visit no**	**1**	**2**	**3**	**4**	**5**	**6**	**7**^ **§** ^
	**Day −7 – 0**	**Day 0**	**Day 1**	**Day 7**	**Week 6**	**Week 12**	**Week 26**
**Visit window**	**Screening**	**Day of surgery**	**± 1 day**	**± 3 days**	**± 1 weeks**	**± 2 weeks**	**± 3 weeks**
Informed consent	X						
Inclusion/Exclusion criteria	X						
Demography	X						
Patient employment status	X						
Medical history	X						
Weight and Height	X						
Physical examination	X						
Vital signs (pulse, blood pressure)	X						
Pregnancy test (women of childbearing potential)	X						
Concomitant medication/therapy	X	X	X	X	X	X	X
Evaluation of CT scan*	X						
Evaluation of X-ray findings*	X		X	X	X	X	X
Randomization	X						
Surgery** (autologous bone graft or treatment with CBVF***)		X					
Procedure information (type and amount of bone graft, hardware used, etc. - time of surgery)		X					
Adverse events	X	X	X	X	X	X	X
Device complaints		X	X	X	X	X	X
Clinical examination (pain, tenderness, warmth and swelling)				X	X	X	X
Documentation of treatments performed outside the trial center****							
Pain medication	X	X	X	X	X	X	X
SF-12v2TM	X			X	X	X	X
Pain (VAS)	X		X	X	X	X	X
End of the trial							X

*Computed tomography (CT) and X-ray assessments are performed as a clinical routine according to the standards of care. They will be not performed for the purposes of the study. **Surgical procedures are performed according to the standard of care. No surgical interventions will be performed for the purposes of the study. ***CBVF, CERAMENT™|BONE VOID FILLER. ****Continuous documentation by patient, when applicable. §These examinations should also be performed at the trial end visit in case the patient prematurely drops out of the trial.

#### V1 - screening visit and randomization

The trial aims and procedures will be explained to the patient by responsible local investigators using a study information booklet. After informed consent is given, the screening visit (V1) will be performed within 7 days prior to day of surgery (day 0). After radiological assessment of the fracture type, baseline demographics, comorbidity, medication, and pregnancy test (if applicable) will be evaluated and verification of inclusion and exclusion criteria performed. The trial participant will be electronically randomized to one of the two treatment arms using a web-based tool. All data will be documented using an electronic case report form (eCRF). Assessment of the VAS and SF-12v2 scores will be performed at the end of the V1.

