## Methods/Design

The CERTiFy (CERament treatment of Tibial Fracture defects) trial is a prospective, open-label, multicenter, controlled, randomized clinical trial. The study will comprise 136 patients with acute traumatic depression fractures of the proximal tibia (limited to AO type 41-B2 & B3) from 13 different trauma centers in Germany. Patients are randomized to receive either an autologous cancellous bone graft taken from the iliac crest or CBVF.

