#### Other endpoints

SF-12v2 PCS and SF-12v2 MCS will be assessed as additional endpoints at visits 4 to 6, the pain measured by VAS (visits 3 to 6) as well as the intake of pain medication at visits 3 to 7. Fracture healing and integrity of the articular surface will be assessed using standard anteroposterior and lateral views of plain radiographs. The radiographs will be reviewed by the panel of two experienced orthopedic trauma surgeons and one consultant who will be blinded as to the kind of material used. The panel will independently review all radiographs in chronological order. The loss of reduction and subsidence of the articular surface will be recorded and analyzed using the Rasmussen score [17], in which articular subsidence, condylar widening, and varus or valgus deviation will be quantitatively assessed over a period of 26 weeks. In addition, the panel will evaluate fracture union, bone defect remodeling as well as loss or premature resorption of the graft using the following point score:

1. Osteolysis, premature resorption of the graft

2. Unchanged size of the void, no resorption of the bone graft

3. Beginning marginal bone defect remodeling

4. Bone defect remodeling with undirected formation of trabecula

5. Bone defect remodeling with directed formation of trabecula

Complications (for example, hardware failure and displacement, wound healing problems, infections, revisions, neurologic impairment, pressure ulcers and others) as well as all adverse events (AE) will be recorded and regularly evaluated throughout the study.

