### Efficacy analysis

Within the primary analysis of this study, SF12v2 summary scores are not normalized to the reference population. Nevertheless, normalized z and t scores of SF12v2 summary scores will be calculated in explorative analyses. SF-12v2 standard 4-weeks recall version will be used within this study. The confirmatory efficacy analysis is planned using a hierarchical testing procedure. In the first step, differences between SF-12v2 PCS are tested by an analysis of covariance (ANCOVA) with SF-12v2 PCS at week 26 as the dependent variable and SF-12v2 PCS at screening, age group (18–39; 40–65), gender, and treatment as covariates. If the covariate-adjusted two-sided 95% confidence interval of the treatment effect within this model (difference of SF-12v2 PCS, experimental treatment group - control group) is located completely above the non-inferiority margin of −5, non-inferiority of CBVF with respect to Physical Component of Quality of Life 26 weeks after surgery will be claimed. The primary endpoint will be primarily analyzed in the PP population. Only if non-inferiority can be claimed in the first step, pain as the co-primary endpoint may be tested in a confirmatory way. Differences between pain assessed by VAS 26 weeks after surgery will be tested by a Wilcoxon-Mann–Whitney-U-Test at a two-sided significance level of 5%. Analysis will be done primarily for the mITT population. Within this hierarchical testing procedure, a global significance level of 5% is ensured. The power was not adjusted since the local power of the second test (pain assessment) is sufficiently large (>99%). In order to check robustness of confirmatory results, supportive analyses of both (co-)primary endpoints will be performed in the mITT, PP and ITT populations. Models with a modified set of covariates (for example, trial site and surgical technique) will also be calculated as supportive analyses. Analyses in the ITT population will require imputing missing data. Multiple imputation methods are planned within this context. Further details will be specified in the Statistical Analysis Plan. All secondary endpoints will be analyzed using appropriate methods depending on the scale of the respective parameter. Analyses of secondary endpoints will be interpreted exploratively.

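### Baseline SF-12v2 is scheduled after randomisation in an open-label trial, so the covariate of the confirmatory ANCOVA could be affected by knowledge of the allocation

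*Protocol article*

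**What the plan says.** In the protocol article, the section on V1 runs through consent, radiology, baseline data and the eligibility check, and then reaches randomisation: "The trial participant will be electronically randomized to one of the two treatment arms using a web-based tool". One general sentence about the eCRF follows, and the section closes with the questionnaires: "Assessment of the VAS and SF-12v2 scores will be performed at the end of the V1". Table 1 ticks randomisation, SF-12v2 and VAS in the same V1 column and gives no order within the visit. Methods/Design calls the study a "prospective, open-label, multicenter, controlled, randomized clinical trial". No section says that the questionnaires come before randomisation or that its result is held back until they are complete.

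Under Efficacy analysis, the confirmatory model is an ANCOVA "with SF-12v2 PCS at week 26 as the dependent variable and SF-12v2 PCS at screening", age group, gender and treatment as covariates. Non-inferiority is claimed if the adjusted 95% interval "is located completely above the non-inferiority margin of −5". Analysis populations admits a patient to the mITT set only if PCS is available both before surgery and at week 26, and the per-protocol set is drawn from the mITT set. On the instrument, Efficacy analysis states: "SF-12v2 standard 4-weeks recall version will be used within this study".

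**The concern.** ANCOVA gives an unbiased treatment effect in a randomised trial because the baseline covariate cannot depend on treatment. A questionnaire filled in after allocation can be known does not have that protection. One arm faces iliac crest harvest, and the article's Background itself stresses the donor-site pain and the effect on quality of life. A patient who has just learned the allocation might answer a self-reported form differently. Adjustment would then carry that difference, multiplied by the regression slope, into the effect that is compared with the margin.

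This test is the gatekeeper: pain is tested in a confirmatory way only if non-inferiority is shown. There is a second, smaller route. A form left blank once the allocation is known would remove a randomised patient from the mITT and per-protocol sets, possibly unequally by arm.

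**Working it through.** **The plan's own figure.** Sample size and power calculation gives a margin of 5, SD 10, true difference 0, one-sided 2.5% and 80% power, with 128 evaluable patients. The noncentral t distribution gives 79.5% power at 63 per arm and 80.1% at 64 per arm, so 128 reproduces. Allowing for 5% ineligible, 128 / 0.95 = 134.7, which gives 135, or 136 as an even number. The stated size is sound. It rests on an unadjusted t-test.

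**Effect of a shifted baseline.** Let d be the between-arm difference in baseline PCS (CBVF minus control) caused by knowing the allocation, and let the slope equal the baseline/week-26 correlation rho (equal SDs).

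- Bias of the adjusted effect = −rho × d
- SE = 10 × √(1 − rho²) × √(2/64), which is 1.73, 1.69 and 1.53 for rho = 0.2, 0.3 and 0.5
- One-sided type I error at a true difference of −5 = 1 − Φ(1.96 − bias/SE)
- Power at a true difference of 0 = 1 − Φ(1.96 − (5 + bias)/SE)

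The documents give neither rho nor d, so both are assumed ranges. Equal allocation, 64 per arm, is also assumed.

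| rho | size of shift | size of bias | type I error if bias favours CBVF | power if bias goes against CBVF (no shift → shift) |
|---|---|---|---|---|
| 0.2 | 1 | 0.2 | 3.3% | 82% → 79% |
| 0.3 | 1 | 0.3 | 3.7% | 84% → 80% |
| 0.5 | 1 | 0.5 | 5.1% | 90% → 84% |
| 0.2 | 2 | 0.4 | 4.2% | 82% → 76% |
| 0.3 | 2 | 0.6 | 5.4% | 84% → 74% |
| 0.5 | 2 | 1.0 | 9.6% | 90% → 74% |

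One line in full, for rho 0.5 and d = −2: bias = +1.0; 1.0 / 1.53 = 0.65; 1.96 − 0.65 = 1.31; upper tail 9.6%.

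**Simulation check** (20,000 ANCOVA runs per scenario, rho 0.5). With d = −2 the bias was +0.99 and the type I error 9.4%. With no shift the type I error was 2.3% and power 90%. With d = +2 the bias was −0.99 and power 73%.

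**After the change.** If the forms are complete before the allocation is known, the expected d is 0 and so is the bias. The type I error stays at 2.5% and the size stays at 128 evaluable, 136 randomised.

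**The case against.** The strongest reply is that disclosure before the forms is inferred. The V1 section is a condensed list, and the article never says that patients learn their allocation before answering. That limits certainty. Even so, the stated order and the open-label design both point that way, and nothing points the other way. Source of bias assigns quality-of-life and pain assessments to surgeons not involved in the operation, which helps with staff influence but not with what the patient knows.

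The second reply concerns size, and much of it stands. With a 4-week recall and same-visit randomisation, nearly all of the recalled period precedes allocation, which should damp any shift. The sample-size section says that one item moved by one category changes PCS by at least 3 points. At 3 points per change, a mean shift of 2 points needs about two-thirds of one arm to change one answer, and a shift of 1 point about one-third. Direction is also open: if control patients report worse on learning that they face harvest, the bias goes against CBVF and costs power.

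Third, Efficacy analysis already plans mITT, per-protocol and ITT analyses, multiple imputation and models with modified covariates. These limit the selection concern, and allocation-dependent missing forms are only a possibility. They do not repair a contaminated baseline, and omitting baseline PCS is not among the examples named.

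Some stronger readings are tempting but not supported:

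- **The pain test is also biased.** Week-26 VAS is tested by Wilcoxon-Mann-Whitney without a baseline covariate, so a late baseline VAS does not enter it.
- **The recall period or the day-7 SF-12 must change.** The article does state "SF-12v2 PCS and SF-12v2 MCS will be assessed as additional endpoints at visits 4 to 6", and at day 7 much of the 4-week window precedes the injury. Those are exploratory endpoints outside the confirmatory hierarchy, and a special recall instruction would depart from the standard version that the plan fixes.

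**Conclusion.** The point holds as a correctable weakness in the order of steps. As written, the baseline PCS that enters the confirmatory model is collected when the allocation can be known, and the plan has no safeguard against that. Over the assumed ranges (shift 1 to 2 points, slope 0.2 to 0.5) the bias is 0.2 to 1.0 points, or 4% to 20% of the 5-point margin. In favour of CBVF, that means a one-sided type I error of about 3.3% to 9.6% in place of 2.5%. Against CBVF, power falls to between 84% and 74%, from 82–90% without a shift.

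These figures illustrate what could happen and do not estimate what has happened. They rest on equal SDs, slope equal to correlation, 64 per arm and an assumed shift. A reader might infer that the primary result is bound to be biased, or biased towards non-inferiority. The documents support neither: they show that the opportunity exists, and say nothing of whether a shift occurs, how large it is or in which direction. The change should be made, but the point does not invalidate the design.

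**What to change.** Reword the V1 section so that SF-12v2 and VAS are completed and entered in the eCRF before the web randomisation is called, or at the least before its result is disclosed. An eCRF check can enforce this. It needs no extra visit and no change to the sample size.

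Trial status says that the study is recruiting, so some baselines may already have been taken after randomisation. Flag those patients, and add a sensitivity analysis of week-26 PCS without the baseline PCS covariate. It gives up the precision gained from the covariate, but the sample size was calculated for an unadjusted comparison, so at 64 per arm it keeps the planned power of about 80%. The cost is a few lines of protocol text, one edit check and one additional table.

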#### V2 - intervention

This visit is intended to document the surgical procedures and procedure-related complications. In both treatment arms the responsible surgeon performs the intervention. The test device is administered according to the instruction for use (IFU) for CBVF. Fracture surgery and, if applicable, harvesting of autologous bone graft will be performed according to the well-established standards of care.

After the surgery, information on the type of surgery, osteosynthesis material, volume of CBVF or autologous cancellous bone graft are documented in the eCRF. Furthermore, adverse events including the device complaints will be documented as well. Postoperative care is performed according to the local SOPs.

#### V3 - day 1 post intervention

Radiographs are taken between day 1 to day 3 to evaluate the quality of reduction of the articular surface as well as the appropriate positioning of the hardware and the device. Furthermore, adverse events including device complaints, the VAS score, and concomitant medication including pain medication will be documented in the eCRF.

#### V4 - day 7 post intervention

The following procedures will be performed: evaluations of the X-rays, monitoring of adverse events including device complaints, the SF-12v2 score, VAS, concomitant medication including pain medication, and clinical healing evaluation (pain, tenderness, warmth, and swelling).

#### V5 - 6 weeks post intervention and V6 - 12 weeks post intervention

Patients will be evaluated in an outpatient clinic by the responsible surgeon. Results of the radiological assessment which is required according to the standard of care will be documented in the eCRF. Possible local complications such as pain, tenderness, warmth, and swelling will be assessed. The number of physiotherapy courses and the need for other therapeutic interventions will be documented in the patient’s diary. Adverse events including device complaint monitoring, the SF-12v2 score, VAS, and concomitant medication including pain medication will be recorded.

#### V7 - 26 weeks post intervention, final visit

The final visit will be performed six months after the intervention. The results of the clinical and radiological evaluation as well as the adverse events and device complaints will be documented in the eCRF. The SF-12v2 score, the VAS score and medication will be assessed and recorded. Computed tomography scans (CTs) and x-rays will be sent anonymously to coordinating investigator for central blinded evaluation.

### Statistics

#### Pre-specification

Details of the statistical analysis of the data collected in this trial will be documented in a Statistical Analysis Plan (SAP) that will be generated by IZKS Mainz and finalized before closing the database. The SAP is based on the protocol including all amendments. The document may modify the plans outlined in this protocol; however any major modifications of the primary endpoint definition and/or its analysis will also be reflected in a protocol amendment. Any deviation from the original SAP must be described and justified in the final report. The statistical analysis will be conducted by means of SAS™.

#### Sample size and power calculation

Sample size was calculated for the primary endpoint (SF-12v2 PCS week 26). Additional power calculations were performed for the co-primary endpoint (VAS pain score week 26). Within the German norm population, mean SF-12v2 PCS is 50 and the standard deviation is 10 [18]. The study population is expected to come very close to this German norm population. Based on the inclusion criteria (age between 18 and 65) and demographic data of the proximal tibia fractures treated at the trial site in Mainz between 2009 and 2011, it seems justified to expect the SF-12v2 PCS results 26 weeks after surgery to be 50 ± 10 (mean ± standard deviation) in both treatment groups. The non-inferiority margin was defined as 5 points on the SF-12v2 PCS scale (range: 0–100). This value is half of the expected standard deviation in the reference population. Since changing one of the SF-12v2 items affecting SF-12v2 PCS by one category causes SF-12v2 PCS to change by at least 3 points, the non-inferiority margin corresponds to less than two items changed by one response category. Under these assumptions, a shifted two-sample t-test with a one-sided significance level of 2.5% and a power of 80% requires 128 patients to show that mean SF-12v2 PCS 26 weeks after surgery in patients treated with CBVF is not more than 5 points lower compared to the control group. Since 5% of randomized patients are expected to be ineligible for the primary Per Protocol Analysis, 136 patients will be randomized. Pain assessed by VAS after 26 weeks is expected to be 2 (80%) or 1 (20%) in the control group and 2 (10%), 1 (20%) or 0 (70%) in the CBVF treatment group. Based on these assumptions, the probability that pain assessed on a VAS comparing one randomly selected patient in each group is higher in the patient treated with CBVF is 14%. A Wilcoxon-Mann–Whitney-Test comprising 128 patients will have a power of >99% to show at a two-sided significance level of 5% that the above specified probability is <50%.

### Analysis populations

The intention to treat (ITT) population comprises all randomized patients, even if the planned surgery/surgeries did not take place. The modified intention to treat (mITT) population includes all randomized patients for which the primary endpoint could be assessed (that is, SF-12 PCS assessment is available both preoperatively and 26 weeks after surgery). Patients are eligible for the per protocol (PP) population, if they fulfill the following criteria: eligible for the mITT population, no violation of inclusion criteria, not meeting any exclusion criteria, trial treatment as randomized, time interval between Visit 2 (day 0, surgery) and Visit 7 (week 26): 22 to 30 weeks, absence of events with a strong effect on quality of life but definitely unrelated to the randomized study treatment (for example, new serious disease during post-operative follow-up, or accident).

The safety population comprises all randomized subjects who received trial treatment (autologous bone graft or Treatment with CBVF). In analyses of the safety population, subjects will be assigned to the treatment they actually received.

### Efficacy analysis

Within the primary analysis of this study, SF12v2 summary scores are not normalized to the reference population. Nevertheless, normalized z and t scores of SF12v2 summary scores will be calculated in explorative analyses. SF-12v2 standard 4-weeks recall version will be used within this study. The confirmatory efficacy analysis is planned using a hierarchical testing procedure. In the first step, differences between SF-12v2 PCS are tested by an analysis of covariance (ANCOVA) with SF-12v2 PCS at week 26 as the dependent variable and SF-12v2 PCS at screening, age group (18–39; 40–65), gender, and treatment as covariates. If the covariate-adjusted two-sided 95% confidence interval of the treatment effect within this model (difference of SF-12v2 PCS, experimental treatment group - control group) is located completely above the non-inferiority margin of −5, non-inferiority of CBVF with respect to Physical Component of Quality of Life 26 weeks after surgery will be claimed. The primary endpoint will be primarily analyzed in the PP population. Only if non-inferiority can be claimed in the first step, pain as the co-primary endpoint may be tested in a confirmatory way. Differences between pain assessed by VAS 26 weeks after surgery will be tested by a Wilcoxon-Mann–Whitney-U-Test at a two-sided significance level of 5%. Analysis will be done primarily for the mITT population. Within this hierarchical testing procedure, a global significance level of 5% is ensured. The power was not adjusted since the local power of the second test (pain assessment) is sufficiently large (>99%). In order to check robustness of confirmatory results, supportive analyses of both (co-)primary endpoints will be performed in the mITT, PP and ITT populations. Models with a modified set of covariates (for example, trial site and surgical technique) will also be calculated as supportive analyses. Analyses in the ITT population will require imputing missing data. Multiple imputation methods are planned within this context. Further details will be specified in the Statistical Analysis Plan. All secondary endpoints will be analyzed using appropriate methods depending on the scale of the respective parameter. Analyses of secondary endpoints will be interpreted exploratively.

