### Eligibility criteria

Patients between the age of 18 and 65 years with a solitary, acute, traumatic, closed depression fracture of the proximal tibia (limited to AO types 41 B2 & B3, Schatzker types II and III) (Figures 2, 3, and 4) requiring reconstruction of the subchondral bone void are enrolled into the trial. The ability to understand the procedure of participating in the study and to comply with the follow-up program is a prerequisite. Only patients with a maximum interval of one week between injury and intervention will be included.

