### Randomization

After giving consent to participate in the study, patients will be randomized by a web-based randomization tool provided by IZKS Mainz allowing investigators to randomize patients via a secure web interface. Randomization will be stratified by age group (18 to 39 years; 40 to 65 years) and gender. Block randomization with variable block sizes will be applied.

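### Optional gain: the confirmatory ANCOVA is valid, but leaving out AO fracture type and age in years may give up a little precision

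*Protocol article*

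**What the plan says.** The Efficacy analysis section of the protocol article models week-26 PCS with screening PCS, age group (18–39 v 40–65), "gender, and treatment as covariates". Non-inferiority is claimed if the adjusted two-sided 95% interval for the treatment difference lies wholly above −5.

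The age and gender terms repeat the randomisation strata in the same coding: "Randomization will be stratified by age group (18 to 39 years; 40 to 65 years) and gender" (Randomization).

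The trial enrols two fracture types: "limited to AO types 41 B2 & B3, Schatzker types II and III" (Eligibility criteria). AO type is neither a stratum nor a model term. It is known in time, because the V1 section describes the work-up before electronic randomisation: "After radiological assessment of the fracture type, baseline demographics, comorbidity, medication, and pregnancy test (if applicable) will be evaluated". Patients whose fracture classification is in doubt are excluded, so the variable should be complete.

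Supportive models with other covariates are planned, with trial site and surgical technique as examples. The Pre-specification section says that major changes to the primary analysis will also appear in a protocol amendment.

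**The concern.** The non-inferiority decision rests on one confidence limit, in a trial planned at 80% power. Baseline variables that predict the outcome narrow that interval when they are in the pre-specified model. Two candidates are already collected.

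- **AO type.** If B2 and B3 fractures recover differently, that difference stays in the residual variance.
- **Age.** A single cut at 40 treats a patient of 40 and one of 65 alike. The Background section links low-energy fractures to older patients with reduced bone density, so age within a group could carry information.

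Screening PCS may not stand in for injury severity. It uses a 4-week recall, and surgery must follow injury within a week, so much of the recall period probably lies before the injury. This is an inference from the schedule, and it does not make screening PCS a poor covariate.

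At stake is some width of the decisive interval. The supportive models cannot recover it, because they do not enter the confirmatory decision.

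**Working it through.** **Inputs from the article (Sample size and power calculation):** SD 10 in both arms, true difference 0, margin 5, one-sided 2.5%, 128 evaluable patients. Allocation of 64 per arm is assumed, since no ratio is stated.

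**1. The plan's own figure.** The article states that "a shifted two-sample t-test with a one-sided significance level of 2.5% and a power of 80% requires 128 patients".
- Standard error = 10 × √(4/128) = 1.768. Non-centrality = 5/1.768 = 2.83.
- Non-central t power with 126 df is 80.15% at N = 128 and 79.5% at N = 126. The stated 128 reproduces.
- This calculation uses no covariates, so the planned power does not depend on the choice discussed here.

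**2. Baseline for comparison.** Three covariates (screening PCS, age group, gender) leave 123 df. With the residual SD held at 10, the half-width is 1.979 × 1.768 = 3.50 and power is 80.1%. Any precision gained from these three covariates is not counted.

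**3. Effect of added terms.** Residual SD = 10 × √(1 − R²), where R² is the assumed share of remaining variance explained by AO type and age in years. With both terms added and age group kept, 121 df remain.

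| Assumed extra R² | Residual SD | CI half-width | Power at N = 128 | N for 80% power |
|---|---|---|---|---|
| current model | 10.00 | 3.50 | 80.1% | 128 |
| 0.02 | 9.90 | 3.46 | 80.9% | 126 |
| 0.05 | 9.75 | 3.41 | 82.1% | 122 |
| 0.10 | 9.49 | 3.32 | 84.1% | 116 |

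If the two terms explain nothing, power moves from 80.13% to 80.12%, a loss of about 0.01 percentage points.

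**4. Which R² is plausible?** The article gives none, so this step is illustrative.
- *Age.* The share of a linear age effect kept by the split is the squared correlation between age and the indicator. For ages uniform from 18 up to the 66th birthday, a fraction p = 22/48 = 0.458 is under 40, and the share is 3p(1 − p) = 0.74. By simulation it is 0.64 for a truncated normal with mean 45 and SD 12, and 0.50 with mean 50 and SD 10. If age explains 2% to 10% of PCS variance, age in years adds between 0.02 × 0.26 = 0.005 and 0.10 × 0.50 = 0.05.
- *AO type.* A difference of d points with a fraction q in one type gives R² = q(1 − q)d²/100. For d = 2 and q = 0.3 this is 0.008. For d = 5 and q = 0.5 it is 0.063.
- *Together:* about 0.01 to 0.11, which gives power of about 80.5% to 84.5% and a half-width of 3.48 to 3.30.

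**5. Chance imbalance.** With half the patients in each type, the between-arm difference in the proportion of B3 has SD √(0.25 × 2/64) = 0.088. A 2-SD imbalance with an assumed 4-point B2–B3 difference moves the estimate by 2 × 0.088 × 4 = 0.71 points. That is 14% of the margin but only 0.71/1.77 = 0.4 standard errors. The same 4-point difference is R² = 0.25 × 16/100 = 0.04, so it already lies within the range in step 3 and is not an additional effect.

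**The case against.** The strongest reply is that nothing in the plan is wrong. The model is pre-specified, adjusts for baseline PCS and for exactly the stratification factors, and is valid for the non-inferiority interval. The sample size claims nothing from covariates. **This stands.**

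The article also gives no evidence that fracture type, or age within the two groups, predicts week-26 PCS once screening PCS is in the model. **This stands.** A reader might infer that the plan definitely gives away precision. The documents show only that it may, and the gain could be near zero.

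A reader might also infer that leaving out fracture type biases the treatment estimate. It does not. Chance imbalance under randomisation already contributes to the residual variance and so to the interval; adjustment only removes that contribution.

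Two further replies carry less weight. The supportive models are open-ended and could include fracture type, but they cannot change the confirmatory conclusion. Changing the confirmatory model in an open-label trial that is already recruiting needs an amendment and a clear record that outcomes were not seen. That is a real cost but a small one, and the article's own amendment rule provides for it.

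**Conclusion.** The point holds as an optional improvement. The confirmatory ANCOVA is sound, but it leaves out one baseline variable and coarsens another, both available before randomisation, and so may be slightly less precise than it could be.

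The size is probably modest: up to about 4 percentage points of power and 0.18 PCS points of half-width if the added terms explain as much as 10% of residual variance, and essentially nothing if they are weakly prognostic. These figures rest on assumed R² values, SD 10, equal arms and a true difference of zero. If the existing covariates already reduce the residual SD, power starts higher and the gain in power points is smaller. The case for acting is the asymmetry between a possible small gain and a negligible loss.

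**What to change.** Before any outcome data are seen, and by protocol amendment with the same wording in the SAP, add two terms to the confirmatory ANCOVA: AO type (41-B2 v 41-B3, as classified at V1) and age in years as a linear term. Keep screening PCS, age group, gender and treatment, so that both stratification factors stay in the model. Retain the current model as a named supportive analysis.

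The cost is two degrees of freedom and a short amendment. No new data are needed, and the margin, sample size and testing order do not change. Age group and age in years will be correlated, which does not harm the treatment estimate, because neither age coefficient is of interest in itself.
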